### Randomization

Participants will be randomly assigned to 1 of the 2 experimental groups or to the control group after the first assessment (at baseline) based on 1:1:1 randomization. The allocation schedule will be generated using an online randomization tool [56], which will be performed and communicated to the patient by an independent researcher. Block randomization will be used with blocks of 9 allocations each. Furthermore, 2 strata will also be used based on age: 1 stratum for 18 to 24 years and another for 25 to 55 years. Participants will be informed about the randomization outcome by email after completing the baseline assessment. Participants in the experimental groups receive a Web link to subscribe free to the intervention with a special code. Afterwards, the participants are required to create an account on the platform with their personal code and self-chosen password. The mobile app will be free to download in the App Store and Google Play Store; however, the intervention will not be open to the general public. Blinding the participants in this RCT will not be possible; however, the statistician is blinded to group assignment.

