**Methods:**

Participants will be recruited through announcements in social media and the Middle East Technical University. Adults (18-55 years) with mild to moderate depressive symptoms (Beck Depression Inventory-II [BDI-II] score between 10-29) will be included in the study. Participants with a medium-to-high suicidal risk (according to the Mini-International Neuropsychiatric Interview) will be excluded. A 3-armed randomized controlled trial with a waiting control group will be utilized. A sample size of 444 participants will be randomized across 3 groups. The first experimental group will receive direct access to the Web version of the intervention; the second experimental group will receive direct access to the mobile app of the intervention as well as automated supportive short message service text messages based on PST. The control group consists of a wait-list and will gain access to the intervention 4 months after the baseline. The intervention is based on an existing PST for the Turkish population, *Her Şey Kontrol Altında* (HŞKA), consisting of 5 modules each with a duration of 1 week and is guided by a clinical psychologist. The primary outcome is change in depressive symptoms measured by the BDI-II. Secondary outcomes include symptoms of anxiety, stress, worry, self-efficacy, and quality of life. Furthermore, satisfaction with, usability and acceptability of the intervention are important features that will be evaluated. All outcomes will take place online through self-assessment at posttest (6-8 weeks after baseline) and at follow-up (4 months after baseline).

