### Recruitment

Recruitment will take place in the general population in Turkey until the end of the project or earlier if the sample size will be achieved. A total of 2 psychologists will be involved in the recruitment, assessments, and therapy delivery: the clinical psychologist will deliver the therapy messages, follow up with the administration of the assessments, message management for admission to the study, and convince dropouts to continue, whereas the other psychologist (Bachelor’s degree) will actively recruit participants for the study. Announcements will be placed online at health-related social media sites and offline at several meeting points at the university. These announcements will contain a link to the research website with detailed information about the study. Respondents who are interested can apply by sending an email to the clinical psychologist. A link to the screening and an informed consent form will be emailed to the respondent. The screening includes the BDI-II and MINI questionnaires; access to a PC and smartphone or tablet; and demographic information of the respondents, such as name, surname, email address, age, and gender. Applicant admission is done by checking the BDI-II and MINI scores of applicants manually.

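### One constant block size of 9 lets some allocations be deduced by the psychologist who treats the active arms and also manages admission

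*Protocol article*

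**What the plan says.** The Randomization section of the protocol article allocates participants "based on 1:1:1 randomization" after the baseline assessment. It fixes the block length: "Block randomization will be used with blocks of 9 allocations each". It also stratifies: "2 strata will also be used based on age: 1 stratum for 18 to 24 years and another for 25 to 55 years". The schedule comes from an online tool, "which will be performed and communicated to the patient by an independent researcher". Of those involved, only the statistician is described as blinded.

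The Recruitment section describes the staff roles: "the clinical psychologist will deliver the therapy messages, follow up with the administration of the assessments, message management for admission to the study". Applicants email this same psychologist. Screening collects demographic items "such as name, surname, email address, age, and gender", so the stratum is known before admission. On eligibility it says: "Applicant admission is done by checking the BDI-II and MINI scores of applicants manually".

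The Intervention Description section adds that the psychologist who gives weekly feedback on homework is the first author of the article.

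**The concern.** With a constant block of 9 and three arms, each block in each stratum holds exactly three places per arm. Someone who knows the block size and the allocations so far can rule out arms as they fill up, and always knows the last place in a block. Custody of the list by an independent person does not prevent this, because the deduction needs only past allocations.

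The psychologist who exchanges messages with participants in both active arms comes to know who they are, and can infer some of the rest to be on the wait-list. The same person manages the messages that bring the next applicant in. At stake is allocation concealment. If the next place can be foreseen, the moment at which an applicant is admitted could be shifted, knowingly or not, toward or away from the wait-list. Participants are not blinded and the primary outcome is self-reported, so later blinding would not offset such selection.

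**Working it through.** The article gives no predictability figure to reproduce, so the bound is worked out from its design.

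**Inputs**
- Block size 9, allocation 1:1:1, two age strata (Randomization). Each block therefore has 3 web, 3 mobile and 3 wait-list places, or 6 active and 3 wait-list.
- 444 participants (abstract, Methods; Sample Size). 444 / 9 = 49.3 blocks.
- Assumption for the bound: the guesser knows the block size, the stratum and every earlier allocation in that stratum before the next admission.

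**Certain allocations.** A place is certain when all places left in the block belong to one arm. The expected number per block is the sum over k of P(the last k places are all the same).
- Three arms: 1 + 2/8 + (2/8)(1/7) = 1 + 0.25 + 0.0357 = 1.29 of 9, or 14.3%. Over 444 participants: 444 × 0.143 ≈ 63.
- Active versus wait-list, with C(9,3) = 84 equally likely arrangements: k = 1 gives 1; k = 2 gives (7 + 35)/84 = 0.5; k = 3 gives (1 + 20)/84 = 0.25; k = 4 gives 10/84 = 0.119; k = 5 gives 4/84 = 0.048; k = 6 gives 1/84 = 0.012. The sum is 1.93 of 9, or 21.4%. Over 444 participants: 444 × 0.214 ≈ 95.

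**Best guess.** Always naming the arm with most places left, the expected number of correct guesses from remaining counts c with total t is G(c) = max(c)/t + Σ (c_i/t) G(c with one fewer in arm i), and G = 0 for an empty block.
- G(3,3,3) = 4.787, and 4.787 / 9 = 53.2%, against 33.3% by chance.
- G(3,6) = 6.548, and 6.548 / 9 = 72.8%, against 66.7% from always naming active.

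**Randomly mixed block sizes.** These rows are simulated. The guesser knows all earlier allocations and which sizes are possible, but not the size of each block. The first row is the exact result above.

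| Block sizes | Certain, three arms | Best guess, three arms | Best guess, active vs wait-list |
|---|---|---|---|
| 9 only | 14.3% | 53.2% | 72.8% |
| 3, 6, 9 | about 4% | about 55% | about 74% |
| 6, 9, 12 | about 2.4% | about 53% | about 72% |
| 9, 12, 15 | about 2% | about 51% | about 71% |

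For 9, 12 and 15, certain calls of active versus wait-list fall from 21% to about 3%. Mixing in blocks of 3 removes most certain calls but raises the average guess rate, because a block of 3 is the most predictable (61% best guess if its size is known). Of these mixes, only 9, 12 and 15 clearly lowers every measure.

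**The case against.** The strongest reply is that the bound is far from practice. No section says the psychologist receives the allocations; the independent researcher tells the participant, by email, after baseline. Participants then create their own account, so the psychologist sees someone in an active arm only once that person registers or sends work. A person not yet seen may be wait-listed, slow to start or a non-starter, and the Limitations section expects high attrition. Wait-list status is thus inferred late and with error. This stands, and it is why the percentages are ceilings and not estimates.

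The second reply is that there is little to steer. Eligibility rests on fixed rules (BDI-II 10 to 29, MINI suicide risk, age, devices). A reader might infer from the manual check that borderline applicants can be accepted or refused at discretion. The text does not support that: it describes checking scores and mentions no judgement. Participants also complete the baseline online themselves, so the psychologist does not fully control the order of randomization. What remains is mainly when admission messages go out.

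A reader might also treat 53% against 33% as the measure of harm. Much of that gain is telling web from mobile. For steering around the wait-list the gain is 72.8% − 66.7% = 6.1 percentage points.

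Finally, the appearance of the block size in the article might be read as disclosure during recruitment. The document does not show that the article was available then. The argument does not need it, since the psychologist is the first author.

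What survives is that the list-holder's independence does not stop deduction, and that one person holds both roles.

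**Conclusion.** The point holds as a minor weakness in allocation concealment. A constant block of 9 makes some places deducible, and the article gives admission messaging to the person best placed to deduce them. The ceiling is 14% certain allocations (21% for active versus wait-list), with a best guess of 53% against 33%, or 73% against 67% for active versus wait-list.

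These figures assume complete and timely knowledge of earlier allocations in the stratum. That the psychologist knows the block size is presumed from authorship, and that this person learns allocations is inferred from the treating role; neither is stated. True predictability is lower by an amount the document does not allow one to calculate. Nothing in it shows that selection took place, or that the list itself was exposed, and neither should be inferred.

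**What to change.** In the Randomization section, replace the single block size with randomly varying sizes in each age stratum, generated by the independent researcher, and avoid blocks of 3; 9, 12 and 15 would serve. State that sizes and sequence are withheld from both psychologists, and leave the sizes out of any document they see. Moving admission messages to someone who does not see who is in treatment would add to this, but needs a change of duties.

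The change itself is a setting in the randomization tool, with no extra participants. The downside is a slightly larger possible imbalance. An unfinished block can leave two arms apart by at most a third of its length: 9/3 = 3 now, 15/3 = 5 with the largest new block. Over two strata that is at most 6 against 10, with 148 planned per arm.

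If recruitment has already finished, the report should say who knew the block size and who could see allocations while admitting applicants.

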### Inclusion and Exclusion Criteria

Turkish participants living in Turkey are eligible if they are aged between 18 and 55 years, have internet access, have both a personal computer (PC) and a smartphone or tablet, and have mild to moderate depressive symptoms (Beck Depression Inventory-II [BDI-II] score between 10 and 29) [35]. Participants will be excluded if they have a BDI-II score above 29 or a medium-to-high suicidal risk (according to the Mini-International Neuropsychiatric Interview [MINI]), and they are advised to contact a psychiatrist or clinical psychologist by sending them an email [36,37].

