#### Primary Outcome: Depressive Symptoms

To measure depressive symptoms as the primary outcome, the Turkish version of the self-report BDI-II will be used at baseline, posttreatment, and follow-up [38]. It has 21 items in total describing depressive symptoms. Each item is scored on a 4-point scale, with a range of 0 (not at all) to 3 (severe). The total score ranges from 0 to 63. The BDI-II has good psychometric properties for online administration [39]. The Turkish version has been proven to have good reliability and validity [38,40]. The cut-off scores are 0 to 9 for minimal, 10 to 29 for moderate, and 30 to 63 for severe depression.

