### Sample Size

In this RCT, 2 experimental groups (receiving the intervention by either the internet or a mobile app) will be compared with a waiting list control group. The sample size is calculated based on an expected difference of Cohen *d*=0.45 (moderate) between 1 of the experimental groups and the control group as in previous studies [22,25]. “ *F* tests-analysis of variance repeated measures” will be applied in G-Power Statistical Power Analysis program version 3.1 and used for sample size calculation [55]. To obtain a power of .80 for a 1-tailed test and an alpha of .05, a total of 234 participants for 3 groups is needed. However, high attrition rates at posttest (25.0%) and at follow-up (30.0%) are expected based on previous studies [24,25]. Therefore, the sample size will be increased to 444 participants in total (allowing an attrition of 25.0%*30.0%=52.5%). This means that 148 participants are required at baseline for each group.

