### Statistical Analyses

The study will be reported in accordance with the consolidated standards of reporting trials guidelines [57]. The data obtained from the study will be evaluated and data tables created using the Statistical Package for Social Sciences version 25.0 statistical software program [58]. The significance level will be accepted as 95% CI (*P*<.05) in all statistical analyses. Quantitative (categorical) variables will be expressed as mean, SD, and upper and lower values in this study, whereas qualitative (continuous) variables will be expressed as numbers (n) and percentage (%). The Kolmogorov-Smirnov Test will be used to examine whether the quantitative data were distributed normally. To measure the efficacy of the treatment in this study, general linear model repeated measures analysis will be used to investigate the change on the primary outcome (BDI-II) scores in dependent variables for the total sample based on the intention-to-treat principle and for analyzing missing data [59]. McNemar tests will be used to measure categorical change as a version of the Chi-square test of independence in repeated measures of dependent groups. Furthermore, the Fisher exact Chi-square tests will be used if the number of crosstabs data is insufficient and the hypothesis is not achieved. Attrition will be defined as not completing any or 1 of the posttreatment measures. The notification effect will be analyzed by comparing the dropout rates of the Web and mobile versions. Finally, the correlation coefficient and statistical significance between the quantitative variables will be calculated by 2-way Pearson correlation analysis.

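### As named, the primary BDI-II model most naturally treats baseline as a time level; stating baseline BDI-II and age stratum as covariates is a free, optional gain in precision

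*Protocol article*

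**What the plan says.** - **Randomization.** Participants are allocated "after the first assessment (at baseline) based on 1:1:1 randomization". Allocation is stratified: "2 strata will also be used based on age: 1 stratum for 18 to 24 years and another for 25 to 55 years".
- **Primary Outcome: Depressive Symptoms.** "the Turkish version of the self-report BDI-II will be used at baseline, posttreatment, and follow-up". One of the three primary-outcome scores is therefore taken before randomisation.
- **Inclusion and Exclusion Criteria.** Entry requires a "Beck Depression Inventory-II [BDI-II] score between 10 and 29". The same scale can range over 0 to 63 afterwards.
- **Statistical Analyses.** "general linear model repeated measures analysis will be used to investigate the change on the primary outcome (BDI-II) scores in dependent variables". No covariate is named and none is ruled out. The section does not say which model term is the primary test, nor whether baseline is a level of time.
- **Sample Size.** The calculation uses a repeated-measures analysis of variance with d=0.45 for one experimental arm against control and gives 234 in total, raised to 444. No correlation between repeated scores is stated.

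**The concern.** The article names a model family and a target, namely change. With three BDI-II scores, a repeated-measures general linear model of change ordinarily takes all three as levels of time. An ordinary model of this kind does not force the arms to share a baseline mean. Its baseline-to-visit treatment contrast is then a difference in mean change scores. Such a contrast subtracts the whole baseline score, whereas adjustment subtracts only the part that predicts the outcome. Unless the regression slope of outcome on baseline is 1, the change score carries extra noise and gives a chance baseline imbalance the wrong weight.

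Age is a design factor with no stated place in the model. Both variables are known for every participant before allocation, so using them costs no patients. That is worth having in a trial that plans for heavy attrition and expects difficult recruitment. What is at stake is the width of the confidence interval, not the validity of the comparison.

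**Working it through.** **Inputs.** From the article: d=0.45; alpha 0.05; 234 participants in 3 groups, so 234/3 = 78 per arm; entry BDI-II 10 to 29. Not in the article, and therefore assumed over a range: r, the correlation of baseline with posttest BDI-II, and k = SD(baseline)/SD(posttest). I take d as standardised by the posttest SD, which the article does not specify.

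**The plan's own figure.** A two-sided comparison of two means by the normal approximation needs 2(1.960+0.842)²/0.45² = 77.5, so 78 per arm and 3×78 = 234. This matches the stated total, although it does not prove how 234 was obtained. The article describes its target as follows: "To obtain a power of .80 for a 1-tailed test and an alpha of .05". One-sided, the same formula gives 2(1.645+0.842)²/0.45² = 61.1, so 62 per arm and 186 in total. That mismatch is a separate matter; two-sided 0.05 is used below. With 148 per arm and 0.75×0.70 = 0.525 retained, 77.7 per arm remain, so 78 is a sensible basis.

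**Variances**, with the posttest SD set to 1:
- change score: 1 + k² − 2rk
- baseline-adjusted: 1 − r²
- difference between them: (k − r)²

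The difference is never negative, so adjustment is at least as precise asymptotically. The two are equal when r = k, that is, when the regression slope r/k is 1. At k=1 the ratio of adjusted to change-score variance reduces to (1+r)/2.

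Example at k=1, r=0.4: 1+1−0.8 = 1.20 against 1−0.16 = 0.84, ratio 0.70. Example at k=0.7, r=0.4: 1+0.49−0.56 = 0.93 against 0.84, ratio 0.90.

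**Power** (noncentral t, 78 per arm, two-sided 0.05, effect 0.45/√variance):

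| k | Quantity | r=0.4 | r=0.5 | r=0.6 |
|---|---|---|---|---|
| any | power, baseline-adjusted | 0.86 | 0.90 | 0.94 |
| 1.0 | power, change | 0.72 | 0.80 | 0.88 |
| 1.0 | variance ratio, adjusted/change | 0.70 | 0.75 | 0.80 |
| 0.8 | power, change | 0.80 | 0.86 | 0.92 |
| 0.8 | variance ratio, adjusted/change | 0.84 | 0.89 | 0.94 |
| 0.7 | power, change | 0.83 | 0.88 | 0.93 |
| 0.7 | variance ratio, adjusted/change | 0.90 | 0.95 | 0.98 |

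**Age stratum.** Nothing in the article says how strongly age predicts BDI-II. If it explained an assumed 1% to 4% of outcome variance, power for a posttest comparison at 78 per arm would move from 0.802 to between 0.806 and 0.818 (normal approximation).

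**The case against.** The strongest reply is that the article is silent rather than committed. It excludes no covariate, and a repeated-measures general linear model can carry covariates and extra between-subject factors. A condensed article may also leave the covariate list to a fuller document. A reader might infer that the plan has decided against adjusting for baseline and age. The text does not support that: baseline as a time level, and a group-by-time test as the primary comparison, are inferences, though natural ones. This part of the reply stands, and it is why the missing age term is not a finding on its own.

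A reader might also infer that the 10 to 29 entry window makes the loss worse by lowering r. That is only half the effect. Truncating baseline may also shrink its SD relative to the untruncated posttest, which lowers k and brings the change score closer to the adjusted analysis. The k=1 row is the most favourable to adjustment of those shown and should not be quoted alone.

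Nor is it right that leaving out age inflates standard errors whenever age predicts symptoms. In a change analysis a stable age effect on level cancels within person; only an age effect on change adds noise. Omission does not bias the estimate.

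Finally, the analysis agrees with the model family used for the sample size, and change-score comparisons in a randomised trial are valid. At k=1 and r=0.5 the change contrast has about the planned 0.80 power. All of that stands. It does not remove the point that a method at least as precise can be had from data already collected.

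**Conclusion.** The point holds as an optional, free gain in efficiency and not as an error. On the natural reading of the named model, the arm contrast is a valid change-score comparison that is no more precise, and usually less precise, than a baseline-adjusted one. Over r of 0.4 to 0.6 the power gained at 78 per arm is 0.14/0.10/0.06 if k=1, 0.06/0.04/0.02 if k=0.8, and 0.03/0.02/0.01 if k=0.7 (differences of the rounded values in the table). These figures rest on assumed r and k, d on the posttest SD, 78 analysed per arm and a two-sided 0.05 test. The age term is probably a small gain.

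**What to change.** In the Statistical Analyses section, state that posttest and follow-up BDI-II are the outcomes, with baseline BDI-II, its interaction with visit, and the age stratum (18–24, 25–55) as covariates, and that the arm contrasts come from this model. A mixed model on all three scores with baseline means constrained equal across arms, plus the age stratum, would serve equally well. Use the same approach for the secondary scales, each with its own baseline. If the intended model already includes these terms, one sentence saying so is enough. The cost is one or two sentences, fixed before unblinding; no extra data or participants are needed.

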### Statistical Analyses

The study will be reported in accordance with the consolidated standards of reporting trials guidelines [57]. The data obtained from the study will be evaluated and data tables created using the Statistical Package for Social Sciences version 25.0 statistical software program [58]. The significance level will be accepted as 95% CI (*P*<.05) in all statistical analyses. Quantitative (categorical) variables will be expressed as mean, SD, and upper and lower values in this study, whereas qualitative (continuous) variables will be expressed as numbers (n) and percentage (%). The Kolmogorov-Smirnov Test will be used to examine whether the quantitative data were distributed normally. To measure the efficacy of the treatment in this study, general linear model repeated measures analysis will be used to investigate the change on the primary outcome (BDI-II) scores in dependent variables for the total sample based on the intention-to-treat principle and for analyzing missing data [59]. McNemar tests will be used to measure categorical change as a version of the Chi-square test of independence in repeated measures of dependent groups. Furthermore, the Fisher exact Chi-square tests will be used if the number of crosstabs data is insufficient and the hypothesis is not achieved. Attrition will be defined as not completing any or 1 of the posttreatment measures. The notification effect will be analyzed by comparing the dropout rates of the Web and mobile versions. Finally, the correlation coefficient and statistical significance between the quantitative variables will be calculated by 2-way Pearson correlation analysis.

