### Measures

Assessments will take place before randomization (baseline), directly after completing the treatment (2 months after baseline), and finally, 4 months after baseline as a follow-up assessment. All outcomes are self-assessed through online questionnaires and can take up to 20 to 30 min to complete. Participants will receive 15 TL (Turkish Lira, the local currency) in total only if completing all 3 assessments. An overview of the measures used per assessment is given in Table 1.

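### The primary analysis is labelled intention-to-treat and is named as the way of handling missing data, but a repeated-measures GLM without imputation is a completer analysis: about 233 of 444 on the plan's own attrition

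*Protocol article*

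**What the plan says.** All references are to the protocol article.

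- **Statistical Analyses.** For efficacy, "general linear model repeated measures analysis will be used to investigate the change on the primary outcome (BDI-II) scores", and this is to be done "for the total sample based on the intention-to-treat principle and for analyzing missing data", with one literature reference attached. The software is the "Statistical Package for Social Sciences version 25.0 statistical software program". No imputation and no likelihood-based method is named.
- **Measures.** BDI-II is taken before randomisation, then "directly after completing the treatment (2 months after baseline), and finally, 4 months after baseline as a follow-up assessment". That makes three repeated values per participant.
- **Sample Size.** The plan states that "high attrition rates at posttest (25.0%) and at follow-up (30.0%) are expected based on previous studies". It raises 234 to 444, "allowing an attrition of 25.0%*30.0%=52.5" per cent, which is 148 per arm.
- **Per-Protocol Analysis.** A separate, secondary set is defined as those with all measurements and, in the experimental arms, all five modules.

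**The concern.** Repeated-measures GLM in SPSS treats the visits as several dependent variables on one row per participant and needs every one of them. A participant with baseline and posttest but no follow-up is removed from the whole model, including the posttest comparison. Unless missing values are filled in first, the procedure therefore analyses completers. It cannot cover the total sample and does not deal with missing data.

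Two things are at stake. Readers would take the result as an analysis of everyone randomised when roughly half were used. In addition, completers may differ between arms. Participants know their allocation, only the active arms have homework and reminders, and only the mobile arm gets daily messages. The plan itself expects those messages to reduce dropout, and so expects attrition to differ by arm.

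**Working it through.** **1. Reproduce the plan's sample size.** Inputs from Sample Size: 234 before attrition, losses of 25% and 30%, 444 randomised.

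- Losses compound: retained = 0.75 × 0.70 = 0.525, so attrition = 47.5%. Then 234 / 0.525 = 445.7, or 446, against the stated 444; the other way round, 444 × 0.525 = 233.1. This agrees closely.
- The printed 52.5% taken as attrition: 234 / 0.475 = 492.6, or 493. It does not agree.
- 30% taken as cumulative: 234 / 0.70 = 334.3, or 335. It does not agree.

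The 52.5% is therefore retention printed as attrition. The sample size counts on about 234 completers, not on 444 analysed.

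**2. What listwise deletion removes** (three BDI-II values in one model; nobody who misses posttest returns for follow-up).

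| Quantity | Losses compound | 30% cumulative |
|---|---|---|
| With posttest | 444 × 0.75 = 333 | 333 |
| With all three values | 333 × 0.70 = 233.1 | 444 × 0.70 = 310.8 |
| Dropped from the model | 444 − 233.1 = 210.9 | 444 − 310.8 = 133.2 |
| Observed posttests discarded | 333 − 233.1 = 99.9 | 333 − 310.8 = 22.2 |

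Taking the printed 52.5% literally as attrition, 444 × 0.525 = 233 would be dropped.

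**3. Compare with the per-protocol set.** Without imputation, the primary set is everyone with all measurements. It differs from the per-protocol set only by the five-module condition, which applies only to the experimental arms. In the wait-list arm the two sets would be identical.

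**4. How much bias?** Simulation of one active arm against control at posttest. From the plan: 148 per arm, d = 0.45, and 25% then 30% dropout. Assumed: SD 8 (so the true effect is 0.45 × 8 = 3.6 points), correlation between visits, and a logit slope for dropout of 0.8 per 8 points in the active arm only. The estimator is the complete-case change score; 2000 trials per scenario, correlation 0.5–0.6:

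| What drives dropout | Mean estimate (true −3.6) | Type I error |
|---|---|---|
| Nothing (random) | no bias | about 5% |
| Baseline drives posttest dropout, and posttest drives follow-up dropout | −3.7 to −3.8 | about 5% |
| Posttest drives follow-up dropout only | −4.3 to −4.5 | 9–10% |
| Baseline drives posttest dropout only | −2.9 to −3.1 | about 8% |

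Over correlations 0.5–0.7 the estimates run from about −2.9 to between −4.4 and −4.5 (the outer end varies a little between runs), with type I error of about 5–11%. A baseline-adjusted analysis of all available posttests returns about −3.6 and about 5%.

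**5. Would any mixed model do?** No. If baseline BDI-II is left out and posttest dropout depends on it, the posttest contrast averages −4.3 to −4.6, with type I error of 10–16%. Including baseline restores −3.6 and about 5%.

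**The case against.** **The plan may intend imputation.** GLM after imputation is a usable intention-to-treat analysis. The missing-data phrase carries a reference that is not at hand, the article condenses a fuller plan, and a separate per-protocol set suggests that the primary analysis was meant to be wider. This stands in part. It rules out saying that a GLM can never serve here. It does not remove the point, because the article names the GLM itself as the means of handling missing data and says nothing of imputation.

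**The model may use only two visits.** The text does not say which visits enter together. A model of baseline and posttest alone would drop 444 − 333 = 111. The conflict with a total-sample analysis remains.

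**A reader might infer that the effect will be exaggerated, by about a quarter, with more false positives.** The documents do not support that. They give neither the SD nor the dropout mechanism. An excess of that size arises in only one of the three severity-driven scenarios; in another there is almost no bias, and in the third the bias is toward the null.

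**A reader might infer that the trial is underpowered.** This is not supported either. It was sized for about 234 completers, so analysing 233 is no shortfall against its own target. Comparing a change score in 233 completers with a baseline-adjusted analysis of 333 changes both the sample and the estimator, so that gap in power is not the cost of deletion alone.

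**A missing-not-at-random analysis is commonly left to the SAP.** Agreed; its absence from the article is not the fault raised here.

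**Conclusion.** The point holds as a contradiction within Statistical Analyses. The named method, without a stated imputation step, cannot deliver the analysis set or the missing-data handling claimed for it. On the plan's own attrition it drops about 211 of 444 (47.5%), or about 133 (30%) if the follow-up figure is cumulative. These counts assume that all three visits enter one model.

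The result would be a completer analysis under an intention-to-treat label. Beyond that, the finding is one of risk: bias may be nil, upward or downward according to what drives dropout, and the simulated range rests on the assumed SD, correlation and slope. Because this is the primary analysis of the primary outcome, the text should be corrected before data are analysed.

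**What to change.** In Statistical Analyses:

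1. Replace the GLM as primary analysis by a linear mixed model for repeated measures (SPSS MIXED, REML, unstructured covariance) with arm-by-visit contrasts at posttest and follow-up. It must include baseline BDI-II. Preferably this is one of the three repeated responses with a common baseline mean across arms, so that all 444 randomised contribute. Otherwise enter baseline as a covariate with its visit interaction; that version uses only participants with a post-baseline value, about 333.
2. Acceptable alternative: keep the GLM, but state that it follows multiple imputation with baseline BDI-II and arm in the imputation model. If the cited reference already means this, one sentence saying so resolves the main conflict.
3. Add one missing-not-at-random sensitivity analysis, for example delta-adjusted multiple imputation by arm, or point to where the SAP specifies it.
4. Keep the complete-case GLM as a sensitivity analysis only, and label it as such.

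In Sample Size, correct the combined attrition to 47.5% (52.5% is retention) and say that the 30% applies to those remaining after posttest.

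Cost: wording only. The software stays the same, and no further participants or data are needed.
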